## Abstract

**Background:**

This study tests whether home visitation to prevent child maltreatment can be improved by adding manualized program components, targeting four key risk factors for child maltreatment: low parental self-efficacy, high levels of perceived stress, parental anger, and post-traumatic stress symptoms. Home visitation is widely implemented, but effects on child maltreatment risk tend to be modest at best. Home visitation tends to be rather flexible (i.e., professionals decide how to support each family). We will test whether adding manualized program components increases program effectiveness, by ensuring that key risk factors are addressed, while maintaining flexibility. In addition, we will test whether any component effects on reduced child maltreatment risk can be explained (i.e., is mediated) by ameliorated risk factors. Lastly, we will test whether the components are more effective for some mothers (e.g., those at highest child maltreatment risk) than for others.

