### Potential differential effects

Not all mothers may benefit equally from these components. On the one hand, mothers who are at highest risk considering the targeted risk factors may benefit more as they have the largest room for improvement [47, 48]. On the other hand, mothers who are at lower risk may benefit more, as they may be more able to engage with program content [49]. Other aspects may also influence the degree to which mothers benefit from the components, such as children’s temperament. For mothers whose child is often frustrated or hard to soothe, it may be more difficult to apply newly learned behaviors (e.g., stay calm when their child upsets them) [50]. However, these mothers may be in greater need for strategies to deal with this child behavior, and thus benefit more from components that target their stress and anger regulation [51]. Furthermore, the accumulation of life events (e.g., quitting one’s job or death of a family member) may either hinder mothers to benefit from the components, if it makes mothers less able to engage with program content [52], or may increase the effectiveness of the components, if they buffer the adverse effects of accumulation of life events [53]. In this study, we will therefore examine maternal (initial levels of targeted risk factors), child (temperament), and family (life events) characteristics as putative moderators of the effects of the manualized components on the targeted risk factors and on risk for child maltreatment. Knowledge on differential effects of the added components can serve to guide personalization of programs. In other words, it can support home visiting programs in their goal to serve individual family needs in an evidence based way.

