### Measures

Table 1 provides an overview of the study variables and their assessment moments. We adapted the wording of some items from the original questionnaires to make them suitable for mothers with low educational levels, using specific guidelines for Dutch texts [61]. Following these guidelines, we tried to keep items short, use an active voice, and avoid using difficult words. For example the phrase ‘I do not do things that I know my child wants me to do,’ was rephrased as ‘I do not do what my child wants me to do.’ With the exception of life events, mothers report on all measures about the last month.

**Table 1 Tab1:** Overview of Study Variables

Outcome	Measure	T1	T2	T3	T4	Reference
Primary outcomes						
Parental self-efficacy	Parenting Stress Index	x	x	x	x	[68]
Levels of perceived stress	Perceived Stress Scale	x	x	x	x	[69]
Parental anger	Parental Anger Scale	x	x	x	x	[70]
Post-traumatic stress symptoms	Post-Traumatic Stress Disorder Checklist – Civilian	x	x	x	x	[65]
Secondary outcomes						
Risk for child maltreatment	Instrument for early identification of Parents At Risk for child Abuse and Neglect	x			x	[54]
Parenting (Rejection, Hostility, Attention, Affection)	Comprehensive Parenting Behavior Questionnaire	x			x	[71]
Potential moderators						
Child temperament (Soothability, Negative emotionality)	Revised Infant Behavior Questionnaire	x				[72]
	Very Short Form of the Revised Infant Behavior Questionnaire					[73]
Life events	Parenting Stress Index	x^a^			x^b^	[68]

*Note.*
^a^ = life events experienced in the past 12 months, ^b^ = life events experienced during the study

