#### Life events

Mothers report how many life events happened to them in the past 12 months and during the study on the ‘life events’-subscale of the Parenting Stress Index (PSI [68]). This subscale consists of thirty yes/no-items such as ‘I got fired/I quit my job’ or ‘I had a miscarriage.’

As most of the questionnaires that we used are copyright protected, we will not publish the data collection forms.

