### Analyses

Prior to analyzing the data, missing data will be handled with multiple imputation. To test whether adding manualized components ameliorates four risk factors (i.e., low parental self-efficacy, high levels of perceived stress, parental anger, and post-traumatic stress symptoms), improves parenting practices, and reduces risk for child maltreatment, we will conduct multivariate analyses of covariance (MANCOVA) and an analysis of covariance (ANCOVA) respectively, with baseline scores (T1) as the covariates, with data of T2, T3, and T4 for the risk factors and data of T4 for parenting practices and risk for child maltreatment as dependent variables.

To test whether amelioration of the targeted risk factors by the added components explains (i.e., mediates) reduced risk for child maltreatment we will conduct a mediation analysis using the PROCESS Macro in SPSS [80]. This macro computes 95% confidence intervals of the indirect effects based on 1000 bootstrap samples. Intervals that do not include 0 indicate a mediation effect.

To test who benefits most from the manualized components we will test whether condition × child, maternal, or family characteristic interaction effects predict ameliorated risk factors and reduced risk for child maltreatment. Putative moderators include mothers’ baseline levels of each of the four risk factors (maternal characteristics), children’s temperament (child characteristic), and the number of life events in the past year and during the study (family characteristic).

We will conduct interim descriptive analyses for our progress annual reports for the study funder. However, no interim analyses that answer the research questions of this study will be conducted. The full protocol, anonymized dataset, and the statistical code that will be used in this study will be available upon motivated request after publication of the results in a peer-reviewed paper.

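### Life events during the study, counted at T4 after both component visits, are listed as a moderator, so that interaction is not a clean test of who benefits

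*Protocol article*

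**What the plan says.** For the fourth study aim, the Analyses section of the protocol article plans to test whether condition-by-characteristic "interaction effects predict ameliorated risk factors and reduced risk for child maltreatment". The family characteristic is "the number of life events in the past year and during the study (family characteristic". The maternal moderators, by contrast, are explicitly baseline values: "Putative moderators include mothers’ baseline levels of each of the four risk factors (maternal characteristics".

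The Life events section confirms that there are two recall windows: "Mothers report how many life events happened to them in the past 12 months and during the study". In Table 1 (Measures) the past-12-months count is marked at T1. The other count is marked at T4, with the note "life events experienced during the study". The Procedure section places T1 one to two weeks before home visit A and T4 one to two weeks after home visit B. The experimental group receives all four components at both visits. The same section says that participants are not blind to their condition.

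The purpose of the moderator analysis is given under Potential differential effects: "Knowledge on differential effects of the added components can serve to guide personalization of programs". The Limitations section repeats it when it speaks of personalised family support.

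**The concern.** Randomisation makes the arms comparable overall and within any subgroup defined by a characteristic that treatment cannot touch. It does not make them comparable within levels of something that happens during treatment. The T4 count is of the second kind, in three respects.

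- The components, or an earlier improvement or worsening in stress or anger, could change how many events occur. One example item is losing or quitting a job.
- Mothers who know their condition could report events differently by arm.
- For a risk factor measured at T2 or T3, part of the count refers to time after the outcome was recorded.

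An interaction with such a count mixes genuine effect modification with the consequences of treatment and of the outcome. The count is also unknown when a nurse decides whether to offer the components, so even an unbiased interaction could not serve the stated purpose of personalising the programme. A misleading claim about which mothers benefit is what is at stake under the fourth aim.

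**Working it through.** **Timing.** Inputs are from the Procedure section: T1 is 1–2 weeks before visit A, T2 is 1–2 weeks after A, T3 is 1–2 weeks before B, T4 is 1–2 weeks after B, and A and B are about three months apart. I take this gap as 13 weeks and assume that the during-study window runs from T1 to T4. Let a = weeks from T1 to A, b = from A to T2, c = from T3 to B, d = from B to T4, each 1 to 2.

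- Whole window: 13 + a + d = 15 to 17 weeks.
- Share after the first component visit: (13 + d)/(13 + a + d), from 14/16 = 88% (a=2, d=1) to 15/16 = 94% (a=1, d=2).
- Share after T2: (13 − b + d)/(13 + a + d), from 12/16 = 75% (a=b=2, d=1) to 14/16 = 88% (a=b=1, d=2).
- Share after T3: (c + d)/(13 + a + d), from 2/16 = 13% (a=2, c=d=1) to 4/16 = 25% (a=1, c=d=2).

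These are shares of time, not of events. They show that the count is almost wholly a post-treatment quantity and that, against a T2 outcome, most of it lies after the outcome. The T1 count has neither problem, because it looks back from before visit A.

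**Trial size used below.** The plan gives no figure for moderation. Its main-effect figure (d = .25, one-sided α = .05, power .80) reproduces: 2 × (1.645 + 0.842)² / 0.25² ≈ 198 per arm, or 396 against the stated 398. It is not in dispute and only sets the scale.

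**Illustration 1: events counted after the outcome.** The inputs are assumed, not from the documents. Each trial has 398 mothers, there are 4,000 trials, and there is no true moderation. Baseline X is standard normal. The outcome is Y = 0.6X − 0.25T + 0.8e. Events M are Poisson with mean exp(log 2 + βY + γT). The fitted model regresses Y on T, X, centred M and T × M, with a two-sided 5% test of the interaction.

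| β (outcome → events) | γ (arm → events) | Interaction rejected | Condition coefficient |
|---|---|---|---|
| 0 | 0 | 5.2% | −0.25 |
| 0.3 | 0 | 4.8% | −0.22 |
| 0.5 | 0 | 5.1% | −0.19 |
| 0 | −0.3 | 4.4% | −0.25 |
| 0.3 | −0.3 | 5.6% | −0.14 |
| 0.5 | −0.3 | 11.7% | −0.06 |
| 0.5 | −0.7 | 21.0% | +0.07 |

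Here γ = −0.3 is a cut in the event rate of 1 − exp(−0.3) = 26%, and γ = −0.7 a cut of 1 − exp(−0.7) = 50%.

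**Illustration 2: shared vulnerability.** Also assumed: Y = −0.25T + 0.5u + e, events Poisson with mean exp(0.3 + kT + 0.35u), 2,000 trials of 398. For k = 0, −0.2 and −0.4 (rate cuts of 0%, 18% and 33%), the condition coefficient in the model with life events is −.251, −.211 and −.180. The interaction test rejects in 4.5%, 4.7% and 4.6% of trials.

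The interaction test is therefore distorted in some plausible structures and not in others. The documents do not say which applies.

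**The case against.** The strongest reply has four parts.

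First, many life events, such as a death in the family or a miscarriage, are unlikely to be altered by two visits with feedback, a relaxation audio and anger cards. If neither arm nor earlier outcome affects events or their reporting, there is no bias. The article also says that mothers do not know the study hypotheses, which softens the reporting argument. This stands, and it is why bias is possible rather than certain.

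Second, the article gives a reason for looking at concurrent events: the components might buffer their harm. That question is legitimate, but it differs from asking who should be offered the components, and randomisation does not protect it.

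Third, the sentence on moderation names no outcome times. T2, T3 and T4 are stated for the main analysis of the risk factors, and maltreatment risk is measured only at T1 and T4. The reversed timing therefore applies only if T2 or T3 risk-factor scores enter the moderation tests. This also stands.

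Fourth, a reader might take the shrinking condition coefficient in the illustrations (16% to 28% for rate cuts of 18% to 33% in the second) as bias in the trial's treatment effect. The plan does not support that reading. Its main effects come from MANCOVA and ANCOVA with T1 scores as covariates and without life events.

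**Conclusion.** The point holds in a limited form. The T4 life-events count is a post-randomisation variable, self-reported by mothers who know their condition. Its interaction with condition is not a clean test of who benefits and cannot guide personalisation. Whether the interaction is actually biased, and by how much, depends on assumptions outside the documents. In the settings examined, the false-positive rate ranged from about 5% to 21%, with the higher values needing both a strong effect of earlier outcomes on events and a cut in the event rate of a quarter to a half. Severity is moderate: one moderator under the fourth aim is affected, while the past-year count, the main comparisons, the sample size and data collection are untouched.

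A reader might also infer that the abstract commits the trial to testing baseline maltreatment risk and that the plan then omits it. The text does not go that far. The abstract offers it as an example ("whether the components are more effective for some mothers (e.g., those at highest child maltreatment risk) than for others"), and the section on Potential differential effects ties highest risk to the targeted risk factors, whose "baseline levels of each of the four risk factors (maternal characteristics" are in the list. What remains is a mismatch in wording: the IPARAN score is collected at T1 but appears in neither list of moderators. Nor can one conclude that the moderator tests lack control of multiple testing, since a condensed article may leave that to the full protocol or analysis plan.

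**What to change.** In the Analyses section, restrict the moderators for the fourth aim to T1 measures: the four risk factors, the two temperament scales and the past-12-months life-events count. Remove the during-study count from that list. Report it by arm as a description, or use it in a separate analysis of buffering that is labelled exploratory and not protected by randomisation, stating which outcome times it is related to.

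Optionally, reconcile the abstract's example with the moderator list, either by adding the T1 IPARAN score or by rewording the example to refer to the targeted risk factors.

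The cost is a change of wording before analysis. All variables are already collected and no questionnaire changes. The price is that the question of whether the components buffer events occurring during the study becomes exploratory.

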## Discussion

Given the serious consequences of child maltreatment, and the typically modest effects of frequently used home visiting programs, it is important to know how programs can be improved to support families by reducing their risk for child maltreatment. This study strives to guide efforts to increase the effects of Supportive Parenting in particular, and the effects of child maltreatment prevention programs in general, by studying whether adding components that target compromised feelings of parental self-efficacy, high levels of perceived stress, parental anger, and post-traumatic stress symptoms, contribute to program effectiveness.

Scholars often seem divided in arguing for either manualized or flexible treatments (for an overview, see [81]). In this study, we bridge both approaches by adding a select set of manualized components while maintaining a level of flexibility. Our study sheds light on whether borrowing some of the advantages of either approach – manualized components to target key risk factors for child maltreatment and the flexibility to adjust program content according to clinical experience – yields larger effects than a more flexible approach.

Research on the effects of a limited set of program components helps us unravel the effects of parenting programs, by identifying the merit of discrete program components, above and beyond other components and common elements [82]. Knowledge on the effectiveness of program components can therefore refine theories about mechanisms of change that underlie program effectiveness.

Understanding whether any effects of the four manualized components on reduced risk for child maltreatment are mediated by amelioration in the four targeted risk factors, improves our understanding of the role of these risk factors in occurrences of child maltreatment. If amelioration of one or more of the targeted risk factors indeed explains a stronger reduction in the risk for child maltreatment yielded by manualized home visitation, this strengthens our theory that these risk factors indeed contribute to risk for child maltreatment [83].

### Limitations

We add four manualized components, based on the premise that these four combined components together increase the effectiveness of home visitation. This approach does not allow us to draw conclusions about the effectiveness of each single component. While it may seem plausible that any effects on, for example, ameliorated parental anger are caused by the component that explicitly targets parental anger, we cannot exclude the possibility that other components (e.g., the one that targets stress) also contributed to the amelioration of parental anger. Thus, the present study only allows for conclusions about the causal effects of all four components combined.

We will test the effectiveness of the manualized components in two home visits. While two sessions may seem insufficient to change key risk factors for child maltreatment that tend to be persistent over time [84, 85], we opted for this approach, first, to reflect the clinical reality of home visiting programs such as Supportive Parenting. We designed this study to inform professionals on how to increase the effectiveness of Supportive Parenting, while maintaining its ease of implementation. The second reason for opting for a two-session approach is that evidence accumulates that interventions with a limited number of sessions (sometimes even single sessions) can yield meaningful effects [86, 87].

Home visiting programs to prevent child maltreatment target a vulnerable group of families. Improving the effectiveness of these programs has the potential to prevent an array of negative outcomes for these families. This study strives to inform both clinical practice and child maltreatment theory. The manualized components that we test in our study are relatively easy to implement into home visiting programs, enabling home visiting programs to disseminate knowledge on the effectiveness of adding these components into clinical practice. In addition, our tests of which mothers benefit most from adding these components can help move the field towards evidence-based personalized family support. Lastly, this study aims to improve our understanding of the role of four key risk factors in reducing risk for child maltreatment, which may contribute to more refined child maltreatment theories.

### Study status

Data collection and recruitment of participants is ongoing.

## Data Availability

Not applicable.

## Appendix

## Abbreviations

ANCOVA: Analysis of covariance
CPBQ: Comprehensive parenting behavior questionnaire
IBQ-R: Revised Infant behavior questionnaire
IPARAN: Instrument for early identification of parents at risk for child abuse and neglect
MANCOVA: Multivariate analyses of covariance
PAS: Parent anger scale
PCL-C: Post-traumatic stress disorder checklist – civilian
PSS-10: Ten-item-version of the Perceived stress scale
PTSD: Post-traumatic stress disorder
